#### **7.2.4.2 Engagement in formal addiction treatment at 30 days**

This variable is defined in the same manner as specified for the primary outcome in Section 7.2.4.1 (engagement in formal addiction treatment at 7 days).

#### **7.2.4.3 Engagement in MOUD at 30 days**

This variable is defined in the same manner as specified in Section 7.2.4.1 for engagement in MOUD at 7 days.

#### **7.2.4.4 Self-reported days of illicit opioid use**

This outcome is measured by TLFB methods at 7 and 30 days. At both visits, the previous 7 days are used for TLFB. The total number of days that the participant noted use of any substances on the F99 form will be counted. Possible values are 0 to 7 days. If substance use is not known for a given day, values will be imputed in two ways: 1) substance use occurred on that day, and 2) substance use did not occur on that day. Both imputation strategies will be analyzed.

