## **8.2 Secondary Effectiveness Outcomes**

1. Engagement in MOUD at 7 days
2. Engagement in formal addiction treatment at the 30 days
3. Engagement in MOUD at the 30 days
4. Self-reported days of illicit opioid use (past 7 days) measured by TLFB methods at 7 and 30 days
5. Craving scores as measured by an analogue visual scale
6. Healthcare service utilization (past 30 days (30 days prior to enrollment), at 30 days post enrollment) measured by Health Services Utilization Form regarding ED visits and hospitalization
7. Satisfaction questionnaires measured by Patient Satisfaction XR-BUP, Patient Satisfaction & Adherence SL-BUP
8. Overdose events past 30 days post enrollment captured by participant self-report, and review of medical records

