### 8.7.7 Timeline Follow-Back (TLFB)

The Timeline Follow-back procedure, will be used to elicit the patient participant's self-reported use, quantity, and route of administration of opioids, marijuana, stimulants, benzodiazepines and alcohol. At enrollment, substance use is reported by the patient participant for the 7-day period prior to informed consent. At the 7-day follow-up assessment, substance use is reported for the 7 days following the ED Index Visit (Day 0). At the 30-day follow-up assessment, substance use is reported for the 7 days prior to study day 30.

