## **2.2.2 Study Assessments**

### **2.2.2.1 Ancillary Component**

A broad array of assessments will be conducted during the index ED visit, daily by telephone/text for 6 days, and in person on Day 7 (range Days 6-10) where the estimated day of ED discharge is Day 0.

Assessments completed at screening include, with electronic case report form (eCRF) in parentheses: ED Health Quiz (EHQ), Diagnostic and Statistical Manual of Mental Disorders (DSM)-5 (DSO), urine drug screen (UDS), COWS (COW), and patient eligibility summary (PES). Along with written informed consent, the following assessments are captured at enrollment: demographics (DEM and DM1), locator information (LOF), other substance use (OSU), TLFB (T99 and F99), health status (HST), and overdose events (ODE). Screening and enrollment assessments are completed at the index ED visit.

Assessments completed pre-injection include vital signs (VTR), assessments related to opioid withdrawal including COW and Objective Opiate Withdrawal Scale (OOW) (Handelsman *et al.*, 1987), pupillary diameter (PPD), craving/desire to use (CRV) (Kozlowski *et al.*, 1989), and bad drug effects (BDE) ([name] *et al.*, 2017). A numerical rating scale pain assessment (PAR) is completed immediately following the injection. The local tolerability scale (LTS) and PAR are completed 30 minutes post injection. Approximately every 30 minutes after the injection for 4 hours (240 minutes), the VTR, COW, OOW, and post injection medications (PIM) assessments are completed. At 240 minutes after the injection, the Adjective Rating Scale for Withdrawal (RSW) (Coloma-Carmona *et al.*, 2019), CRV, BDE, PAR, and LTS are completed.

Assessments completed by telephone/text on Days 1-6 include desire to use and daily substance use.

Assessments for the Day 7 visit include UDS, COW, ODE, an injection site assessment (ISR), satisfaction survey (S99), health services utilization (HS1, HS2, HSI, and HSO), engagement in treatment (ETP), and a study completion assessment (STC).

Ongoing and as needed during the study, adverse events (AEs), serious adverse events (SAEs), and protocol deviations are collected on the AD1, AD2, AD3, PDR, and PDV forms.

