#### 7.2.4 Definition of Secondary Outcome Measures

The secondary outcomes are defined below and will be analyzed for the ITT population only.

The following are considered the key secondary outcomes and will be analyzed by the DSC:

1. Engagement in MOUD at 7 days
2. Engagement in formal addiction treatment at the 30 days
3. Engagement in MOUD at the 30 days
4. Self-reported days of illicit opioid use (past 7 days) measured by TLFB methods at 7 days
5. Self-reported days of illicit opioid use (past 7 days) measured by TLFB methods at 30 days

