#### **7.2.5.4 Self-reported days of illicit opioid use**

Counts of self-reported illicit opioid use will be compared between treatment groups at both 7 and 30 days using negative binomial regression. These models will include treatment and covariates for outcomes measured at baseline as well as site, age, sex, ethnicity, race, treatment seeking, and insurance status (see **Exhibit 2**). Linear contrasts will be used to estimate treatment differences along with 95% confidence intervals for XR vs. SL at each follow-up time.

| Exhibit 2: Covariates for Primary and Secondary Outcomes |                        |                           |                                                                  |
|-----------------------------------------------------------------|------------------------|---------------------------|------------------------------------------------------------------|
| Covariate                                                | Variable name   | Coding in analysis | Comments                                                  |
| Treatment                                                       | COREVARS.TRT           | categorical               | XR-BUP, SL-BUP                                                   |
| Visit                                                           | VISNO                  | categorical               | Day 7, Day 30                                                    |
| Site                                                            | DEM.SITE               | categorical               |                                                                  |
| Age                                                             | DEM.DEBRTHDT           | continuous                | Age at randomization                                             |
| Sex                                                             | DEM.DESEX              | categorical               | Male, Female                                                     |
| Ethnicity                                                       | DEM.DEHISPNC           | categorical               | Hispanic, Non-Hispanic, Unknown/not reported                     |
| Race                                                            | DEM.WHITE, DEM.DEBLACK | categorical               | Black, White, Other, Unknown/not reported                        |

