**Exhibit 3: Power (N = 850 per group) for Variations of Difference in Treatment Engagements Between SL-BUP and XR-BUP**

[figure not shown]

For secondary outcomes such as self-reported days of illicit opioid use, craving, and satisfaction scores, this sample size will provide 90% power to detect relatively small standardized differences (Cohen's  $d = 0.16$ ) between the two intervention groups. Figure 2 below shows detectable risk

ratios for different proportions of participants with an overdose event within 30 days in the SL-BUP treatment arm, which is not expected to be high. If the proportion is 15%, there will be sufficient power to detect a risk ratio of 0.70 and if it is 2%, there will be sufficient power to detect a risk ratio of 0.25.

**Exhibit 4: Detectable Risk Ratios for Overdose Outcome as a Function of Proportion of Participants with Overdose Events in the SL Group (80% Power)**

[figure not shown]

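### SAP 7.2.4.4 defines the key secondary outcome of illicit opioid days as days with use of any substance, which contradicts the outcome's name; the negative binomial model is a smaller, conservative problem

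*Combined protocol and SAP*

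**What the plan says.** Protocol 8.2 lists the secondary outcome as "Self-reported days of illicit opioid use (past 7 days) measured by TLFB methods at 7 and 30 days". SAP 7.2.4 makes it two of the five key secondary outcomes, one for each visit; the first is "Self-reported days of illicit opioid use (past 7 days) measured by TLFB methods at 7 days". The heading of SAP 7.2.4.4 keeps that name.

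The counting rule under that heading does not: "The total number of days that the participant noted use of any substances on the F99 form will be counted". It continues: "Possible values are 0 to 7 days". The imputation rule that follows, for days on which use is unknown, also speaks of substance use and not of opioid use.

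Protocol 8.7.7 says that the timeline follow-back elicits "self-reported use, quantity, and route of administration of opioids, marijuana, stimulants, benzodiazepines and alcohol".

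SAP 7.2.5.4 returns to opioids and names the model: "Counts of self-reported illicit opioid use will be compared between treatment groups at both 7 and 30 days using negative binomial regression". Protocol 12.6.3.3 names the same model. Neither section states a robust variance or a fallback distribution for this outcome. On power, SAP 10.2 says: "For secondary outcomes such as self-reported days of illicit opioid use, craving, and satisfaction scores, this sample size will provide 90% power", at a Cohen's d of 0.16.

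**The concern.** An outcome named for opioids has an operative rule that counts four other classes of substance as well. If the rule is programmed as written, a participant who stops opioids completely but uses cannabis or alcohol every day scores 7 at both visits. The result would be reported as an effect on illicit opioid use without being one. Participants held at 7 by other substances also carry no information about the treatment, so a real effect on opioid days would be diluted.

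The rule is also silent on prescribed opioids. Under protocol 8.4.9 the SL-BUP arm receives a daily buprenorphine prescription, while the XR-BUP arm receives one injection. If the form recorded prescribed buprenorphine as use, the count would differ between arms for a reason unrelated to illicit use.

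The model is a separate and smaller matter. A negative binomial distribution has no upper limit, and this count stops at 7. When the distribution does not fit, the model-based standard errors need not match the true sampling variation.

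**Working it through.** **Step 1: the plan's own power figure.** Inputs from SAP 10.2: 850 per arm, two-sided 0.05, d = 0.16. Power = Φ(d·√(n/2) − 1.96), with √425 = 20.616. This gives Φ(0.16 × 20.616 − 1.96) = Φ(1.34) = 0.91. The stated 90% reproduces for a comparison of two means; the exact d for 90% is (1.960 + 1.282)/20.616 = 0.157.

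**Step 2: dilution by the any-substance rule.** The documents give no mean, SD or share of non-opioid users, so these are assumptions: opioid days average 2.45 versus 2.00 with SD 0.45/0.16 = 2.81. A share f in each arm, unrelated to opioid use, uses a non-opioid on all seven days and so scores 7. For an arm with opioid mean m and SD s:

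- observed mean M = 7f + (1 − f)m
- observed variance V = 49f + (1 − f)(s² + m²) − M²
- diluted d = (1 − f) × 0.45 / √(average of the two arms' V)

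For f = 20%, the means are 3.36 and 3.00 and the variances 9.64 and 10.33 (average 9.98). So d = 0.36/√9.98 = 0.114, and power = Φ(0.114 × 20.616 − 1.96) = 0.65.

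| Daily non-opioid users | Difference in days | Average variance | d | Power |
|---|---|---|---|---|
| 0% | 0.45 | 7.91 | 0.160 | 91% |
| 20% | 0.36 | 9.98 | 0.114 | 65% |
| 40% | 0.27 | 10.23 | 0.084 | 41% |
| 60% | 0.18 | 8.65 | 0.061 | 24% |

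A second set of assumptions (3.0 versus 2.6 days, SD 2.5, control-arm variance) gives 80%, 55%, 34% and 19% at f = 10%, 30%, 50% and 70%. The pattern does not depend on the particular means chosen.

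**Step 3: the negative binomial standard error.** Counts from 0 to 7 were simulated from a beta-binomial distribution with 850 per arm, no treatment effect and no covariates, 600 runs per case. Each data set was fitted by maximum likelihood with a common dispersion α. The model-based standard error of the log mean ratio is √[(1/m₀ + α)/n + (1/m₁ + α)/n]. At mean 3.5 and within-person correlation 0.3, α averaged 0.164, so it is √[2(0.286 + 0.164)/850] = 0.0325, against an empirical 0.0300: a ratio of 1.08. Ratios of model-based to empirical standard error:

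| Mean days | Corr. 0 | 0.1 | 0.3 | 0.5 | 0.7 |
|---|---|---|---|---|---|
| 1.05 | 1.05 | 1.02 | 1.10 | 1.21 | 1.39 |
| 2.10 | 1.15 | 1.06 | 1.08 | 1.23 | 1.43 |
| 3.50 | 1.44 | 1.16 | 1.08 | 1.17 | 1.31 |
| 4.90 | 1.81 | 1.49 | 1.09 | 1.07 | 1.20 |
| 6.30 | 3.31 | 2.50 | 1.80 | 1.59 | 1.42 |

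High correlation means counts split between 0 and 7. Low correlation with a middle or high mean means counts vary less than a Poisson count, which the model cannot represent. Type I error with the model-based standard error was 0.000 to 0.047; with a sandwich standard error it was 0.035 to 0.065. A further run of 300 data sets at mean 1.4 and correlation 0.2 gave a ratio of 0.98. The simulation error there is about 1/√600 = 4%, so that ratio cannot be told from 1.

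**Step 4: power of the two standard errors at d = 0.16** (1,000 runs per case). Over control means of 2.1 to 4.9 days and correlations of 0.3 to 0.7, model-based power was 0.74 to 0.89. At a control mean of 6.3 and correlation 0.3 it was 0.38. Sandwich power was 0.89 to 0.94 throughout.

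**The case against.** **F99 may hold only opioids.** The SAP's form list shows two forms, T99 and F99, both labelled only as timeline follow-back, plus a supplement and an assessment-period form. Protocol 8.7.7 describes the procedure as a whole, not F99. With the section heading, the key secondary list and the analysis section all saying opioids, a loosely worded sentence is as plausible as a wrong endpoint. This stands as a caveat: a reader might infer that the trial will certainly count cannabis or alcohol days, and the documents do not show that. Nor do they show the reverse. Even an opioid-only form would leave prescribed buprenorphine unaddressed.

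**The SAP is not final.** SAP section 14 calls the randomised-trial section of version 3.0 a first draft, to be finalised in version 4.0 before database lock. That does not cure the sentence, but it means that there is a planned occasion to correct it.

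**The dilution figures are assumed.** They are. The documents give no prevalence, and use on all seven days is the simplest case. The figures illustrate sensitivity and do not predict a result.

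**The model criticism can be pushed too far.** A reader might infer that the negative binomial model produces false positives, or that the stated 90% power is simply not delivered. Neither is supported. No inflation of type I error appeared in the cases run, and the power loss depends on a distribution that the documents do not give. The simulations also leave out the baseline outcome, site and other covariates in the planned model. Protocol 12.6.1 promises diagnostic tests and sensitivity analyses in general terms. The 90% figure is an illustration for several outcomes; the trial is sized on the primary outcome. All of this stands, and it makes the model a secondary matter.

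**Conclusion.** The definition is wrong as written. SAP 7.2.4.4 contradicts protocol 8.2, SAP 7.2.4, SAP 7.2.5.4 and its own heading, and it affects two of the five key secondary outcomes. Its practical size depends on what F99 records and on how many participants use non-opioids daily, neither of which is documented. Under the stated assumptions the loss is large: power for a true d of 0.16 is roughly 65% with 20% daily non-opioid users and 24% with 60%.

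The model is imperfect in a conservative direction. Its standard errors are too wide by a few percent to about 10% for moderately overdispersed counts, by about 20% to 40% for counts split strongly between 0 and 7, and by more when counts pile up near 7. The two problems compound, because an any-substance count moves the mean towards 7.

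The documents leave open whether prescribed buprenorphine enters the count, so a bias between arms is possible but not shown.

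**What to change.** In SAP 7.2.4.4, before version 4.0 is finalised and before database lock:

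1. Define the count as the number of the seven days with illicit (non-prescribed) opioid use, and say explicitly that buprenorphine and other opioids taken as prescribed do not count.
2. Name the form and variables used, as the SAP already does for medication engagement, craving and satisfaction.
3. Reword both imputation rules so that they refer to opioid use on the unknown day.

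In SAP 7.2.5.4, as an inexpensive improvement, keep the mean ratio and the planned covariates but state that standard errors and confidence intervals are empirical (sandwich).

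The cost is a few sentences and a few lines of code. The timeline follow-back already elicits opioids as their own class, so no new data collection appears necessary; whether the form separates prescribed from illicit opioids should be confirmed. Making the change before lock avoids choosing between two versions of the outcome with the data in hand.

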## 12.6 Statistical Methods

### 12.6.1 General Approach

Nominal and ordinal categorical variables will be summarized using frequencies and percentages. Continuous variables will be summarized with the following descriptive statistics: N, mean, standard deviation, median, minimum, maximum, interquartile range, and range.

No imputation of missing data will be performed in the primary and secondary analyses. Diagnostic tests and sensitivity analyses will be performed. For evaluation of effectiveness, all analyses will follow the intention to treat principle including all patients in their randomized group regardless of treatment received.

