#### **7.2.7 Missing Data**

Several strategies were imposed to accommodate the likelihood that missing data will occur during this study including prevention, strict data collection procedures, careful selection of variables without large proportions of missing values, and regular monitoring of the trial. Despite these prevention efforts it is reasonable to assume missing data will occur. Our proposed primary and secondary analyses make use of all available data and are valid under the assumption that missing data will be missing at random (MAR) (Diggle, et al., Molenberghs, et al.). We may evaluate the plausibility of this assumption by determining the extent of missing data and use logistic regression to identify factors associated with missing data. We may conduct sensitivity analysis using a pattern-mixture approach implemented using multiple imputation under missing not at random (MNAR) assumptions to examine the robustness of conclusions of the primary analysis to missing data (Little, et al., Molenberghs, et al.).

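### For two key secondary outcomes the SAP fills every unknown day of opioid use in two opposite ways, although the protocol rules out imputation, and it names no main result

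*Combined protocol and SAP*

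**What the plan says.** Protocol 12.6.1 (General Approach) states: "No imputation of missing data will be performed in the primary and secondary analyses". The next sentence adds: "Diagnostic tests and sensitivity analyses will be performed". Protocol 12.6.7 mentions imputation only as an optional MNAR sensitivity analysis of the primary analysis.

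SAP 7.2.7 (Missing Data) agrees, and names MAR as its assumption: "Our proposed primary and secondary analyses make use of all available data and are valid under the assumption that missing data will be missing at" (the quote stops just short of the end of that clause).

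SAP 7.2.4.4 defines the outcome as a count of days ("Possible values are 0 to 7 days") and builds imputation into that definition. For a day with unknown use, "values will be imputed in two ways: 1) substance use occurred on that day, and 2) substance use did not occur on that day". It then says: "Both imputation strategies will be analyzed".

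SAP 7.2.4 lists the outcome twice among the five key secondary outcomes: "Self-reported days of illicit opioid use (past 7 days) measured by TLFB methods at 7 days", and "Self-reported days of illicit opioid use (past 7 days) measured by TLFB methods at 30 days". SAP 7.2.5.4 specifies negative binomial regression at each visit, without saying which filled version it uses.

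**The concern.** The protocol and SAP 7.2.7 lead the reader to expect an available-data analysis. SAP 7.2.4.4, followed as written, produces only two single-value-imputed analyses per visit, neither of which is the analysis the protocol describes. Nothing ranks the two or calls either a sensitivity analysis.

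Two versions at two visits make four tests. SAP 9.2 assesses all p-values at 0.05 and does not adjust secondary analyses for multiplicity. If the versions disagree, the plan does not say which result answers the question, so the choice could be made after the data are seen. The filled days also enter the model as if they had been observed, so the standard errors ignore the uncertainty about them.

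**Working it through.** **1. The texts side by side**

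| Place | Rule for secondary analyses |
|---|---|
| Protocol 12.6.1 | No imputation; sensitivity analyses allowed |
| Protocol 12.6.7, SAP 7.2.7 | All available data, MAR; imputation only as an optional MNAR sensitivity analysis |
| SAP 7.2.4.4 | Each unknown day filled as use, then as no use; both analysed |
| SAP 7.2.5.4 | Negative binomial model at each visit; version not stated |
| SAP 16.2 (output list) | Sensitivity table for the primary outcome only |

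Elsewhere the SAP does rank such rules. In the Ancillary component, worst-case imputation is the main handling (SAP 7.1.1), and complete-case and best-case analyses are sensitivity analyses (SAP 7.1.4). That ranking is missing here.

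**2. The plan's own figure for this outcome**

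Inputs: d = 0.16 with 90% power (protocol 12.4.1); 850 per arm and two-sided 0.05 (protocol 12.3); 1:1 allocation (protocol 8.4.4).

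Power = Φ(d × √(n/2) − 1.96) = Φ(0.16 × √425 − 1.96) = Φ(1.34) = 0.910. The stated 90% reproduces.

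In days, d = 0.16 is 0.16 × SD. The documents give no SD. For assumed SDs of 2.0, 2.5 and 3.0 days it is 0.32, 0.40 and 0.48 day.

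**3. What the two rules do to the treatment difference**

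Let u be the share of unknown days in an arm and M the mean days of use per 7 implied by the known days.

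- No-use version: arm mean = (1 − u) × M
- All-use version: arm mean = (1 − u) × M + 7u

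The treatment difference (XR − SL) under all-use minus that under no-use is 7 × (u_XR − u_SL), whatever the values of M. For a gap of k percentage points this is 0.07k days: 0.14 at 2 points, 0.42 at 6 and 0.70 at 10. All of these gaps are assumptions.

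**4. Illustration**

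Assumed M: 2.0 days (XR) and 2.5 days (SL), a known-day difference of −0.50 and a rate ratio of 0.80.

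| Unknown share, XR / SL | Difference, all-use | Difference, no-use | Rate ratio, all-use | Rate ratio, no-use |
|---|---|---|---|---|
| 0% / 0% | −0.50 | −0.50 | 0.80 | 0.80 |
| 10% / 10% | −0.45 | −0.45 | 0.85 | 0.80 |
| 5% / 15% | −0.92 | −0.23 | 0.71 | 0.89 |
| 15% / 10% | −0.20 | −0.55 | 0.93 | 0.76 |

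Second row in full: all-use 0.9 × 2.0 + 0.7 = 2.50 and 0.9 × 2.5 + 0.7 = 2.95; no-use 1.80 and 2.25.

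**5. The two versions do not bound the effect**

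Both arms receive the same fill. At 10% unknown in each arm both versions give −0.45, but opposite fills in the two arms would give 1.80 − 2.95 = −1.15 and 2.50 − 2.25 = +0.25.

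**The case against.** The strongest reply is that paired use and no-use fills are naturally sensitivity analyses, which protocol 12.6.1 allows, and that the RCT part of the SAP is still to be finalized in version 4.0 before database lock. The second part stands, and it makes the change cheap. The first does not settle the matter. SAP 7.2.4.4 is a definition section, it does not use the label, and it offers no unimputed version to which the fills could be sensitivity analyses.

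Three stronger readings are tempting, and the documents do not support them.

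- **That every dropout is scored 7 days in one version and 0 in the other.** At the planned 15% dropout this would move an arm mean by 0.15 × 7 = 1.05 days. But the rule concerns use on a given day on the TLFB form, which reads most naturally as filling gaps in an existing calendar. SAP 7.2.7 would then govern participants without one. Where this SAP imputes a whole missing outcome, as in the Ancillary component, it says so. The text sets no explicit limit, so the scope still needs stating. The 15% is an allowance for sizing the primary outcome, not a share of unknown days, and a shift common to both arms cancels in the mean difference.
- **That the choice of fill alone can create or erase the detectable effect.** This needs an unequal dropout split and an SD that the documents do not give. Take 12% and 18% unknown, no true effect and an assumed mean of 2.5 days in both arms. The difference (12% arm minus 18% arm) is 0.88 × 2.5 − 0.82 × 2.5 = +0.15 under no-use and 0.15 − 0.42 = −0.27 under all-use. The two lie 0.42 apart, but neither reaches 0.40 in size.
- **That the reported effect would be one of two extremes.** The SAP plans to run both versions, and they are extremes of each participant's count, not of the treatment effect (step 5).

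**Conclusion.** The conflict is explicit and needs no outside source: protocol 12.6.1 and SAP 7.2.7 on one side, SAP 7.2.4.4 on the other. For two of the five key secondary outcomes the SAP leaves out the promised available-data analysis and puts two unranked imputed analyses in its place.

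How much this matters numerically cannot be determined from the documents. There is no effect if all days are known. With equal unknown shares, both versions shrink the mean difference by the same factor (1 − u), and only the rate ratio can differ between them. With shares k points apart, their mean differences are 0.07k days apart. The means, unknown shares and SDs used above are assumptions for illustration. The primary outcome is not affected. The change is worth making before lock, chiefly so that one result per visit is fixed in advance.

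**What to change.** In SAP 7.2.4.4 and 7.2.5.4:

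1. Name the available-data negative binomial analysis as the reported key secondary result at each visit. One way is to count use over known days with log(known days) as an offset, so that a partial calendar needs no fill. This treats a participant's unknown days as similar to the known ones, in keeping with the MAR statement in SAP 7.2.7.
2. Label the all-use and no-use versions as sensitivity analyses, and do not describe them as bounds on the treatment effect.
3. State that the fills apply only to unknown days in a started calendar, not to participants with no TLFB at that visit.
4. Report the share of unknown days by arm and visit, so that readers can judge how far the two versions could diverge.

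Inverse-probability weighting is optional. Neither protocol 12.6.3.3 nor SAP 7.2.5.4 calls for it on this outcome.

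The cost is a few sentences in SAP version 4.0 and one additional model at each visit. No new data collection is needed, and the protocol needs no amendment because the change restores its rule.
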